**Table 6 Subgroup analyses for primary outcomes**

| Outcome and sub-group                 | Betamethasone
N = | Placebo
N = | Unadjusted RR
or HR (95% CI) | Adjusted RR
or HR (95% CI) | P value | Interaction
P value |  |
|---------------------------------------|----------------------|----------------|---------------------------------|-------------------------------|---------|------------------------|--|
| Cardiometabolic risk factor composite |                      |                |                                 |                               |         |                        |  |
| Trial protocol                        |                      |                |                                 |                               |         |                        |  |
| Standard-dose treatment               |                      |                |                                 |                               |         |                        |  |
| Double-standard dose treatment        |                      |                |                                 |                               |         |                        |  |
| Multiple Pregnancy                    |                      |                |                                 |                               |         |                        |  |
| Singleton                             |                      |                |                                 |                               |         |                        |  |
| Multiple                              |                      |                |                                 |                               |         |                        |  |
| Infant sex                            |                      |                |                                 |                               |         |                        |  |
| Female                                |                      |                |                                 |                               |         |                        |  |
| Male                                  |                      |                |                                 |                               |         |                        |  |
| Tocolytic used                        |                      |                |                                 |                               |         |                        |  |
| Ethanol                               |                      |                |                                 |                               |         |                        |  |
| Salbutamol                            |                      |                |                                 |                               |         |                        |  |
| Both                                  |                      |                |                                 |                               |         |                        |  |
| None                                  |                      |                |                                 |                               |         |                        |  |
| Reason for preterm birth              |                      |                |                                 |                               |         |                        |  |
| Unplanned preterm birth               |                      |                |                                 |                               |         |                        |  |
| Hypertensive disorders of pregnancy   |                      |                |                                 |                               |         |                        |  |
| Rh iso-immunisation                   |                      |                |                                 |                               |         |                        |  |
| Placenta praevia                      |                      |                |                                 |                               |         |                        |  |
| Diabetes mellitus                     |                      |                |                                 |                               |         |                        |  |

|                                                         |  |  |  |  |  |  |
|---------------------------------------------------------|--|--|--|--|--|--|
| Time to first major adverse cardiovascular event |  |  |  |  |  |  |
| Trial protocol                                   |  |  |  |  |  |  |
| Standard-dose treatment                                 |  |  |  |  |  |  |
| Double-standard dose treatment                          |  |  |  |  |  |  |
| Multiple Pregnancy                               |  |  |  |  |  |  |
| Singleton                                               |  |  |  |  |  |  |
| Multiple                                                |  |  |  |  |  |  |
| Infant sex                                       |  |  |  |  |  |  |
| Female                                                  |  |  |  |  |  |  |
| Male                                                    |  |  |  |  |  |  |
| Tocolytic used                                   |  |  |  |  |  |  |
| Ethanol                                                 |  |  |  |  |  |  |
| Salbutamol                                              |  |  |  |  |  |  |
| Both                                                    |  |  |  |  |  |  |
| None                                                    |  |  |  |  |  |  |
| Reason for preterm birth                         |  |  |  |  |  |  |
| Unplanned preterm birth                                 |  |  |  |  |  |  |
| Hypertensive disorders of pregnancy                     |  |  |  |  |  |  |
| Rh iso-immunisation                                     |  |  |  |  |  |  |
| Placenta praevia                                        |  |  |  |  |  |  |
| Diabetes mellitus                                       |  |  |  |  |  |  |

Relative risk, Hazard ratio

**Table 7 Subgroup analyses for secondary outcomes**

| Outcome and sub-group | Betamethasone
N = | Placebo
N = | Unadjusted RR,
HR or mean
difference (95%
CI) | Adjusted RR,
HR or mean
difference
(95% CI) | P value | Interaction |
|------------------------------|------------------------------|------------------------|------------------------------------------------------------------|----------------------------------------------------------------|----------------|--------------------|
| Secondary outcome     |                              |                        |                                                                  |                                                                |                |                    |
| Trial protocol        |                              |                        |                                                                  |                                                                |                |                    |
| Standard-dose treatment      |                              |                        |                                                                  |                                                                |                |                    |

|                                     |  |  |  |  |  |  |
|-------------------------------------|--|--|--|--|--|--|
| Double-standard dose treatment      |  |  |  |  |  |  |
| Multiple Pregnancy                  |  |  |  |  |  |  |
| Singleton                           |  |  |  |  |  |  |
| Multiple                            |  |  |  |  |  |  |
| Infant sex                          |  |  |  |  |  |  |
| Female                              |  |  |  |  |  |  |
| Male                                |  |  |  |  |  |  |
| Tocolytic used                      |  |  |  |  |  |  |
| Ethanol                             |  |  |  |  |  |  |
| Salbutamol                          |  |  |  |  |  |  |
| Both                                |  |  |  |  |  |  |
| None                                |  |  |  |  |  |  |
| Reason for preterm birth            |  |  |  |  |  |  |
| Unplanned preterm birth             |  |  |  |  |  |  |
| Hypertensive disorders of pregnancy |  |  |  |  |  |  |
| Rh iso-immunisation                 |  |  |  |  |  |  |
| Placenta praevia                    |  |  |  |  |  |  |
| Diabetes mellitus                   |  |  |  |  |  |  |

Relative risk, Hazard ratio, Mean difference

**Table 8 Sensitivity analyses**

| Primary or secondary outcome                                                | Betamethasone
N = | Placebo
N = | Unadjusted
RR, HR or
mean
difference
(95% CI) | Adjusted RR,
HR or mean
difference
(95% CI) | P value |
|-----------------------------------------------------------------------------|----------------------|----------------|-----------------------------------------------------------|------------------------------------------------------|---------|
| Using questionnaire data only                                        |                      |                |                                                           |                                                      |         |
|                                                                             |                      |                |                                                           |                                                      |         |
| Using per protocol analysis                                          |                      |                |                                                           |                                                      |         |
|                                                                             |                      |                |                                                           |                                                      |         |
| Including additional covariates in the statistical model |                      |                |                                                           |                                                      |         |
|                                                                             |                      |                |                                                           |                                                      |         |

| Excluding participants for whom the reason for preterm birth was listed as maternal diabetes mellitus            |  |  |  |  |  |
|------------------------------------------------------------------------------------------------------------------|--|--|--|--|--|
| Diabetes mellitus (any type)                                                                                     |  |  |  |  |  |
| Type 2 diabetes mellitus                                                                                         |  |  |  |  |  |
| Type 1 diabetes mellitus                                                                                         |  |  |  |  |  |
| Gestational diabetes mellitus                                                                                    |  |  |  |  |  |
| Excluding participants for whom there was a known family history of diabetes mellitus noted at 30 year follow-up |  |  |  |  |  |
| Diabetes mellitus (any type)                                                                                     |  |  |  |  |  |
| Type 2 diabetes mellitus                                                                                         |  |  |  |  |  |
| Type 1 diabetes mellitus                                                                                         |  |  |  |  |  |
| Gestational diabetes mellitus                                                                                    |  |  |  |  |  |

Relative risk, Hazard ratio, Mean difference, Adjusted for current BMI, sex, current socioeconomic status, gestation at birth and birthweight z score in the adjusted analysis

Table 9 Sensitivity analysis for win-odds hierarchical outcome analysis excluding those with fetal death or death before 28 days

| Outcome | Betamethasone
N = | Placebo
N = | Odds Ratio
(95% CI) | P value |
|---------|----------------------|----------------|------------------------|---------|
|---------|----------------------|----------------|------------------------|---------|

|                                              |  |  |  |  |
|----------------------------------------------|--|--|--|--|
| Win-odds
Hierarchical
outcome |  |  |  |  |
|----------------------------------------------|--|--|--|--|

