## 5. Study outcomes

Outcome definitions and the hierarchical approach to different data sources have been detailed in a supplementary document (S1). This supplemental document may be amended separate to this analysis plan and will be finalised after blinded review of the data with the aim of optimising the validity of outcome definitions. All outcomes for this analysis plan will use one of three denominators as indicated by the following superscript designation:

a Denominator will be all participants whose mothers were randomised in the original trial.

b Denominator will be all participants alive at 28 days of age.

c Denominator will be all participants who consented to this follow-up study with data available for the outcome.

s indicates outcomes for which a separate analysis will be undertaken using only self-reported data (see section 10).

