#### 5.1. Primary outcomes

1. Composite of cardiovascular risk factors cs. Any of:
  - Diabetes mellitus or prediabetes
  - Hypertension
  - Dyslipidaemia
2. Age at first major adverse cardiovascular event bs. Earliest of:
  - Age at first admission for myocardial infarction or coronary revascularisation
  - Age at first admission for peripheral vascular disease (acute limb ischaemia or revascularisation)
  - Age at first admission for stroke
  - Age at first heart failure admission
  - Age at cardiovascular death

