### **Additional Secondary Outcomes**

- Ischaemic heart diseasecS
- StrokecS
- Peripheral vascular diseasec
- Overweight or obesitycS
- BMI (continuous)cS
- Death from any causea
- Self-reported general healthcS
- Rate of admissions to hospital with respiratory illness as the primary reason for admission/per patient year of followupc
- Chronic respiratory illness (Self-reported diagnosis of asthma or COPD, self-reported chronic respiratory symptoms, admissions for asthma or chronic obstructive pulmonary disease [COPD] or prescription of pharmaceuticals for asthma or COPD)c
  - AsthmacS
  - COPDcS
  - Chronic respiratory symptomscS
  - Admissions for asthma or chronic obstructive pulmonary disease (COPD)c
  - Prescriptions of pharmaceuticals for asthma or COPDc
- Highest level of educational attainmentcS

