#### 4.3. Approach for withdrawals, missing data and outliers

Data up to the point of withdrawal will be used for those participants who have withdrawn from the study unless they have withdrawn their consent for use of their data. No imputation will be performed for missing data. We do not plan to exclude outliers from the analysis. Sensitivity analyses will be performed to assess the impact of missing data on the primary and secondary outcomes.

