### 4.8. Sensitivity analyses

The following sensitivity analyses will be performed to examine the primary and secondary outcomes:

- Excluding participants for whom there were protocol deviations (per protocol analysis)
- Including current BMI, sex, current socioeconomic status, gestation at birth and birthweight z score (1) in the adjusted analysis

In addition, the following sensitivity analyses will be performed for diabetes outcomes

- Excluding participants for whom the reason for preterm birth was listed as maternal diabetes mellitus
- Excluding participants for whom there was a known family history of diabetes mellitus noted at 30 year follow-up

For the secondary outcome *Hierarchical win ratio outcome* a sensitivity analysis will be performed using time to death after 28 days, excluding those with fetal death or death before 28 days from the analysis.

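### The extended-covariate sensitivity model relies on current BMI and current socioeconomic status, so it drops deaths before the 50-year data collection and cannot serve the mortality and MACE outcomes

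*SAP*

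**What the plan says.** Section 4.8 (under section 11, Exploratory analyses) opens its first list with "The following sensitivity analyses will be performed to examine the primary and secondary outcomes". One item on that list is "Including current BMI, sex, current socioeconomic status, gestation at birth and birthweight z score (1) in the adjusted analysis". Table 8 in the appendix repeats the covariate list in footnote 4: "Adjusted for current BMI, sex, current socioeconomic status, gestation at birth and birthweight z score in the adjusted analysis". Neither place exempts an outcome.

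The outcomes in scope use three denominators, set out in section 5:

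- **Denominator a:** "Denominator will be all participants whose mothers were randomised in the original trial". It covers "Death from any cause" and time to death after randomisation.
- **Denominator b:** everyone alive at 28 days. It covers the primary MACE outcome, for which section 5.1 lists "Age at cardiovascular death" as one of the qualifying events, and the secondary outcomes on cardiovascular death.
- **Denominator c:** those who consented to this follow-up and have data. It covers BMI, which is itself a secondary outcome.

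On missing values, section 4.3 states "No imputation will be performed for missing data". The main adjusted model in section 4.5 uses gestational age at randomisation, plus further baseline variables if they differ markedly between groups.

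**The concern.** Two of the five covariates are measured at about age 50, while several of the outcomes are deaths at any time from randomisation onwards. For those outcomes the covariates are absent because the event occurred. A regression without imputation then removes the cases themselves. This is a separate matter from whether variables arising after randomisation should be adjusted for at all.

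For the mortality outcomes, a planned row of Table 8 could not be filled. For MACE, a number would appear, but for a different outcome in a different population: non-fatal events in people who survived and responded. A difference between that number and the main result could come from the added covariates, the lost events or the changed sample, and the plan gives no means of telling them apart.

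**Working it through.** **1. Who can have the covariates.** BMI carries superscript c in section 5.2, so the SAP counts it only for consenters with data. Current socioeconomic status is not defined, and section 4.1 lists government data sources from which it might be drawn. That does not help, because a missing BMI alone removes a record. A fetal death, a neonatal death or any later death before the 50-year contact has no current value of either covariate.

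**2. What the model does with them.** With no imputation, the regression uses complete cases. It therefore moves every outcome, whatever its stated denominator, to a subset of consenters.

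| Outcome | Denominator | Removed by the extended model | What is left |
|---|---|---|---|
| Death from any cause; time to death | a | All deaths before 50-year data collection; all non-consenters | Only deaths after the 50-year data were given |
| Cardiovascular death (age at; proportion) | b | As above, among those alive at 28 days | As above |
| MACE (primary) | b | Fatal events; earlier non-fatal events in people who later died; non-consenters | Mainly non-fatal MACE in surviving responders |
| Risk-factor composite, BMI and others | c | Consenters lacking BMI or socioeconomic status | A smaller set than the main model uses |

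**3. Whether other text repairs it.** Section 4.3 promises missing-data sensitivity analyses but does not specify them. The enriched sample in section 11 adds 30-year data to outcomes and denominators, not to covariates. No rule carries an earlier BMI or socioeconomic value forward. The two addenda change clustering, one sensitivity exclusion and the risk-factor composite, but not this model. Section 4.8 does write outcome-specific rules elsewhere (two analyses for diabetes outcomes, one for the win ratio), so a restriction here would fit its style.

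**4. Estimability of the mortality outcomes.** An illustration with assumed death rates (25% control, 18% treated; 1,200 people) had 152 deaths in 611 and 109 in 589. After records without BMI were dropped, 0 deaths in 459 and 0 in 480 remained. The log-binomial fit was not identified (standard error for treatment about 35,000). The zero follows by construction; the fit shows only that the software returns nothing usable.

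**5. MACE: the plan's own figure first.** Section 9 gives N = 420, 8% with an event, HR 0.33, two-sided 5% and 90% power. Events = 420 × 0.08 = 33.6. With 1:1 allocation (assumed), Schoenfeld's formula gives

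power = Φ(√(33.6/4) × |ln 0.33| − 1.96) = Φ(2.898 × 1.109 − 1.96) = Φ(1.25) = 89.5%,

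which reproduces the stated 90%.

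**6. MACE: events lost.** The SAP does not give the share of MACE cases who have died before data collection, so a range is assumed:

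| Share lost (assumption) | Events left | Power at HR 0.33 |
|---|---|---|
| 0% | 33.6 | 89.5% |
| 10% | 30.2 | 86.2% |
| 20% | 26.9 | 82.0% |
| 30% | 23.5 | 76.7% |

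The base of 420 is the planning figure for participants able to be located. MACE is counted in everyone alive at 28 days, so these are indications of scale and not forecasts of counts. Loss of non-consenting survivors comes on top and is not included.

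**The case against.** Several points on the other side stand.

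- **The loss is not strictly total.** Someone who gave 50-year data and died before the data cut-off has values. The SAP does not define what counts as current, and the supplement on outcome definitions and data sources (S1) is not at hand. The supportable statement concerns deaths before the 50-year data collection.
- **The stakes are limited.** This is one sensitivity analysis under the exploratory heading. No main result changes.
- **The loss is not hidden.** Table 8 has its own N per arm and its own unadjusted column, so a smaller sample can be seen. For mortality, a model without events fails openly. Table 8 does not say, however, whether the unadjusted column uses the reduced sample.
- **Refitting the main model on the same records is good practice** and does not correct an error in the text.

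A reader might infer more: that a real effect on fatal MACE would disappear and be credited to BMI or socioeconomic status. One can construct this. Let f be the fatal share, non-fatal events be equal by arm, and fatal events split 2:1. With nf = 33.6(1 − f)/2 and x = 33.6f/3, RR = (nf + 2x)/(nf + x), which is 1.07 at f = 0.1 and 1.22 at f = 0.3. Deleting fatal cases returns 1.00. But the fatal share, the 2:1 split and the equal non-fatal counts are all assumed, and the base is again the 420. The shift is also small against sampling error: SE(log HR) is about 2/√33.6 = 0.345, so ln 1.07 to ln 1.22 is about 0.2 to 0.6 standard errors. The documents support the loss of events, not a bias of known size or direction.

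What the objections leave untouched is the mechanism: the covariates are unavailable for deaths before data collection, imputation is barred, and no outcome is exempted.

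**Conclusion.** The point holds for this one sensitivity model. As specified, it cannot give a risk ratio or hazard ratio for death from any cause, time to death or cardiovascular death, because essentially no events remain. For MACE it yields an estimate of something other than the primary outcome. Non-consenters are dropped from all denominator a and b outcomes as well. The conclusion rests on the SAP's own denominators, its bar on imputation and the reading that the model applies to every primary and secondary outcome, which is the natural reading of section 4.8.

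The number of MACE events lost cannot be derived from the document; the 10% to 30% range is an assumption. The main adjusted analysis in section 4.5 stands as written.

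**What to change.** In section 4.8 and in Table 8 footnote 4:

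- Restrict current BMI and current socioeconomic status to denominator c outcomes.
- For denominator a outcomes, use only sex from the list.
- For denominator b outcomes, use sex and, if the sponsor keeps birth covariates, gestation at birth and birthweight z score. In people alive at 28 days, both are fixed before the outcome and do not depend on survival or response at 50 years.
- For denominator c outcomes, refit the main adjusted model on the same complete cases and show it beside the extended model, so that the two differ only in covariates.

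The cost is a change of wording and one extra fit per denominator c outcome, with no new data. The downside is that no estimate adjusted for BMI or socioeconomic status will be shown for mortality or MACE; the present rule cannot validly give one.
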